### Adverse events

2.12

AEs are defined as negative clinical manifestations following the treatment, and adverse reactions are defined as drug-related AEs. Participants can report AEs via WeChat at any time. We will record the occurrence time, severity, duration, measures taken, and outcomes of AEs in the CRF. AEs will be divided into mild, moderate, and severe. The causal relationship between AEs and drugs will be judged as affirmative, very likely, possible, suspicious, or impossible. Mild to moderate adverse reactions will be continuously tracked by the research team. Once judged as a serious adverse reaction, it will be reported to the Ethics Committee, and the participant's trial will be terminated immediately. When a participant begins to show an emergency, the principal investigator will read the participant's emergency letter, give appropriate treatment based on the drug taken and the symptoms that appear, and record the reason for unblinding.

### Quality control of data

2.13

All researchers will receive training courses to remember the standard operation procedure. In addition, they will need to master the screening of eligible participants, the use of CRS, the distribution and recording of the drugs, data filling, and other matters. They should also fill in CRFs in accordance with uniform requirements. Once the CRFs are formed, they cannot be changed; any additional revisions should be described, signed, and dated in time. Any subsequent amendments, along with the accompanying material provided to the patient, will be submitted to the Research Ethics Committee. During the trial, an independent Data Monitoring Committee will be set up to check the following issues: whether the contents of CRFs are consistent with the original data; whether the participants meet the inclusion criteria; the signatures of the participants’ informed consent; and the distribution, storage, and recording of drugs. In addition, we will maintain the dropout rate below 20% by communication through WeChat.

### Data collection and management

2.15

In week 0, week 2, and week 4, all demographic data and outcome measures will be recorded in CRFs according to the description of patients, and the angina-relevant indices will be exported in an excel from the WeChat background and filled in the CRFs. Since patients have to fill in their “angina treatment diary” every day, the accuracy and reliability of angina-related indicators are guaranteed. The researchers will also send private messages to participants to remind them of their fillings, which will guarantee their participation. The researchers will check the photos of DLT taken daily to ensure patient compliance with the medication regimen. After the data monitor and auditors have checked the CRF contents, 2 independent students will enter data separately in EpiDate software (Version 3.1), and the statistician will check the consistency of the 2 pieces of entered data. The Trial Steering Committee will convene a meeting to evaluate the blindness and the completion of the trial, and then lock the database.

### Statistical analysis

2.16

Statistical analyses consist of 3 parts—baseline comparability analysis, efficacy analysis, and security analysis. An independent statistician will be in charge of the analyses, and Statistical Analysis System (version 9.2) will be used. All tests are 2-sided, and *P* < .05 is considered to indicate statistical significance. According to the intention-to-treat principle,^[32]^ there will be 3 analysis sets: the full analysis set, the per-protocol analysis set, and the safety analysis set. Participants who insist in taking medication for 2 weeks will be involved in the full analysis set group; if a critical variable is missing in any given case, the statistician will consider the last observation result as the final data. Patients who conform to the treatment plan will be included in the per-protocol analysis set group. The Mantel–Haenszel Chi-squared test and analysis of covariance will be conducted in the case of important baseline non-comparability. Normally distributed quantitative data will be presented as mean ± standard deviation and analyzed by Student *t* test. Non-normally distributed quantitative data will be presented as median and interquartile range and analyzed by the Kruskal–Wallis test. Ordinal data, like ECG efficacy, will be analyzed by the Kruskal–Wallis test. Qualitative data will be presented as percentage and rate and analyzed by the Chi-square test and Fisher exact test. The paired Student *t* test will be used to analyze significant differences between pre- and post-treatment. Moreover, subgroup analysis will be conducted according to gender, age, and complications to explore the internal consistency of the conclusions. For the safety analysis, the statistician will adopt the safety analysis set to evaluate the incidence rate of AEs and the change of laboratory indices. Both AEs and laboratory indices are described in lists and analyzed by the chi-square test or Student *t* test.

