### Removal and discontinue criteria

2.5

A participant will be removed under the following circumstances:

(1)violations of the inclusion and/or exclusion criteria;(2)refusal to undergo required examinations;(3)failure to take drugs during the treatment period;(4)myocardial infarction or sudden cardiac events.

A participant has the right to drop out at any time during the treatment; however, his or her reasons for withdrawal must be recorded in the case report form (CRF). According to the intention-to-treat principle, their last data will be involved in the final analysis. Under the following circumstances, the trial might be discontinued:

(1)participants begin to have serious adverse reactions after taking DLT;(2)participants begin to show high sensitivity to the medication, such as headache, stomach ache, diarrhea, and other discomforts;(3)masking and randomization fail.

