### Randomized design, blinding, and allocation concealment

2.6

In order to reduce selection bias and balance various non-research factors among groups, we will adopt a randomized block design and allocation concealment. The participants will be randomized in a 1:1 ratio into the DLT group and the placebo group, in 4 blocks of 19 participants. Random numbers from 1 to 76, as well as group numbers, will be generated by Statistical Analysis System software in CRS managed by the Clinical Evaluation Center of the China Academy of Chinese Medical Science. After inputting a participant's information into CRS, a random number will be generated. After the participant signs informed consent, the researcher obtains the corresponding group number from CRS. Neither of the participants and researchers will be allowed to know the random numbers and group numbers. In order to keep the study double-blind, DLT and the placebo will have the same appearance, smell, taste, and weight. The allocation will not be revealed until the end of the study, unless serious adverse events (AEs) happen. If an individual begins to show serious adverse reactions, the case will be reported to the Ethics Committee, and the blinding will be uncovered by the principal researcher. Then the participant will be removed from the study, and the related data will be recorded. If the emergency events exceed 20% of the sample content, the clinical trial will be discontinued, and the results will be deemed invalid.

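### The full analysis set is called intention-to-treat but requires 2 weeks of medication, contradicts the drop-out rule in Section 2.5, and leaves no efficacy set with all randomised participants

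*Protocol article*

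**What the plan says.** Section 2.16 (Statistical analysis) states that, under intention-to-treat, "there will be 3 analysis sets: the full analysis set, the per-protocol analysis set, and the safety analysis set". It then sets the entry condition for the first: "Participants who insist in taking medication for 2 weeks will be involved in the full analysis set group". The per-protocol set consists of those who followed the treatment plan. The safety set serves adverse events and laboratory values. The article does not say which set carries the primary outcome.

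Section 2.5 (Removal and discontinue criteria) gives participants the right to leave at any time during treatment and continues: "According to the intention-to-treat principle, their last data will be involved in the final analysis". The same section lists grounds for removing a participant, among them "failure to take drugs during the treatment period" and "myocardial infarction or sudden cardiac events". Section 2.6 adds removal after unblinding for a serious adverse reaction, with the related data recorded.

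On missing data, Section 2.16 says: "if a critical variable is missing in any given case, the statistician will consider the last observation result as the final data". The primary outcome in Section 2.8.1 is the change in angina frequency from baseline to week 4. Table 3 schedules angina frequency at day 0, week 2 and week 4, and the diary is sent every night.

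**The concern.** Intention-to-treat protects the comparison because membership of the analysed groups is fixed by randomisation alone. Two weeks of medication is half of the 4-week treatment period, and whether a participant completes it can depend on tolerability, lack of benefit or an event. Section 2.5 itself anticipates discomforts such as headache, stomach ache and diarrhoea on the medication. Blinding does not prevent such effects from causing unequal stopping.

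The rule is also not settled. A participant who stops in week 1 is in under Section 2.5 and out under Section 2.16. If that is still open when the data are unblinded, the choice can be made with the result in view. At stake is whether the effect reported as intention-to-treat compares the randomised groups or only those who stayed on treatment for two weeks.

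**Working it through.** **1. The passages side by side**

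| Participant | Section 2.5 | Section 2.16, full analysis set |
|---|---|---|
| Drops out in week 1 | Last data analysed | Excluded |
| Drops out in week 3 | Last data analysed | Included, last observation used |
| Removed before week 2 | Data use not stated | Excluded |
| Removed after week 2 | Data use not stated | Meets the 2-week condition |

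The first row is a direct contradiction. The third follows from the 2-week condition itself, whatever removal means for the data. The per-protocol set does not supply an all-randomised set, so the conclusion does not depend on which efficacy set is primary.

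**2. Inputs from Section 2.11**

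Planned difference 0.65 attacks per week; SDs 0.45 and 1.03; dropout at most 20%; 76 participants, 1:1. The dropout step reproduces: 30 / 0.8 = 37.5, rounded up to 38 per arm, and 2 × 38 = 76. Pooled SD = √((0.45² + 1.03²)/2) = 0.795.

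**3. Shift caused by the exclusion**

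If k of 38 in an arm are excluded and average e attacks per week more than those kept, that arm's mean falls by (k/38) × e. The documents give no exclusion rates by arm, so k and e are assumptions.

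- k = 4, e = 1, one arm only: 4/38 = 0.105; 0.105/0.65 = 16%.
- k = 6, e = 1, one arm only: 6/38 = 0.158; 0.158/0.65 = 24%.
- 4 in one arm and 2 in the other, e = 1: (4 − 2)/38 = 0.053; 8%.
- Equal k and e in both arms: 0.

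The shift flatters whichever arm loses more of its worse participants, so it can favour Danlou tablet or placebo.

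**4. Effect on the test**

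Simulation: t test, no true effect, 38 randomised per arm, SD 0.795, two-sided 5%, 10,000 runs per setting. Exclusion was given a chosen correlation with a worse outcome. Bias is the absolute shift in attacks per week; each cell gives bias, then type I error.

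| Excluded, arm A / arm B | Correlation 0 | 0.3 | 0.5 | 1.0 (extreme) |
|---|---|---|---|---|
| 20% / 0% | 0.00, 5.1% | 0.09, 7.0% | 0.14, 11.4% | 0.28, 36.0% |
| 20% / 10% | 0.00, 4.9% | 0.04, 6.1% | 0.06, 6.7% | 0.13, 15.6% |
| 20% / 20% | 0.00, 4.7% | 0.00, 5.3% | 0.00, 5.6% | 0.00, 10.2% |

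Bias therefore needs both imbalance and a link with outcome.

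**5. Room in the sample size**

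With the document's SDs and two-sided 5%, t-test power for 0.65 is 94.0% with 38 per arm analysed and 87.6% with 30 per arm. The first figure assumes that outcomes are obtained for everyone and that the difference is not diluted by participants who stop the drug.

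**The case against.** The best defence is that the harm is conditional. Unequal stopping unrelated to outcome causes no bias, equal stopping causes almost none, and a 20% versus 10% split at moderate correlation moves the type I error only to 6% or 7%. The one-arm illustration is deliberately unfavourable: 1 attack per week is 1/0.795 = 1.26 SD, and the plan's 20% is a ceiling for the whole trial, not for stopping before week 2. All of this stands, and it limits what can be said about size. It does not remove the contradiction or supply an all-randomised set.

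Four stronger readings are tempting, and the documents do not support them.

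- A reader might infer that the rule favours Danlou tablet whenever stopping differs by arm. If more placebo participants stop for lack of benefit, excluding them flatters placebo.
- A reader might take removal under Sections 2.5 and 2.6 to mean deletion from the analysis. Neither section says so, and someone removed in week 3 already meets the 2-week condition. Infarction is not a component of the primary outcome, and adverse events have their own analysis.
- A reader might count last observation carried forward as a further breach of the randomised comparison. It excludes nobody; it is a separate source of bias, in either direction. An expected placebo response, which might be cited against it, is nowhere in the article.
- Section 2.6 says that if emergencies exceed 20%, "the clinical trial will be discontinued, and the results will be deemed invalid". That concerns whether the trial stands as a whole, not who is compared in a completed analysis, and is no part of this point.

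**Conclusion.** The point holds in this form. The full analysis set in Section 2.16 rests on a post-randomisation adherence condition, is mislabelled as intention-to-treat, and contradicts Section 2.5 for anyone who stops before week 2. This is stated text, not something left to an unseen analysis plan.

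The size is conditional. With 4 to 6 of 38 excluded in one arm only, each with 1 attack per week more than the rest, the shift is 0.11 to 0.16 per week; with balanced exclusion it is close to nil. Neither the direction nor the actual amount can be read from the documents.

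A lesser point also stands: under the stated rule "the statistician will consider the last observation result as the final data", so an earlier value replaces the week-4 value and is treated as observed, although week-2 and nightly diary data are collected.

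**What to change.** 1. In Section 2.16, define the full analysis set as all randomised participants, analysed in the arm assigned, with no minimum exposure. Use the 2-week or adherence condition only for the per-protocol set.
2. Reconcile Section 2.5 with this definition, so that a participant who stops before week 2 is handled the same way in both places.
3. State in Sections 2.5 and 2.6 that data of removed participants are retained, and that diary follow-up is sought where the participant agrees. The rules on stopping treatment stay as they are.
4. Secondarily, replace last observation carried forward with a repeated-measures model on baseline, week-2 and week-4 values, or on weekly diary counts. Keep last observation carried forward at most as a sensitivity analysis.

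The cost is wording, a little more analysis work and continued nightly messages for those who agree. The 76 randomised need not increase on this account. The estimate may come out less favourable.

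### The full analysis set in section 2.16 requires 2 weeks on medication, so early stops are dropped after randomisation, against the intention-to-treat principle that 2.16 and 2.5 invoke

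*Protocol article*

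**What the plan says.** Section 2.16 (Statistical analysis) names three sets under intention-to-treat: full analysis, per-protocol and safety. It gives one entry rule for the first: "Participants who insist in taking medication for 2 weeks will be involved in the full analysis set group". For missing values it adds: "if a critical variable is missing in any given case, the statistician will consider the last observation result as the final data". The per-protocol set needs conformity to the treatment plan, and the safety set serves adverse events and laboratory indices. No other efficacy set is defined.

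Section 2.5 (Removal and discontinue criteria) takes a different line on dropouts. It says "A participant has the right to drop out at any time during the treatment" and then "According to the intention-to-treat principle, their last data will be involved in the final analysis". The same section lists removals, among them "failure to take drugs during the treatment period" and "myocardial infarction or sudden cardiac events". After unblinding for a serious adverse reaction, section 2.6 says "Then the participant will be removed from the study, and the related data will be recorded". Section 2.12 says that on a serious adverse reaction the participant's "trial will be terminated immediately".

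The primary outcome in section 2.8.1 is the change in angina frequency from baseline to week 4, taken from a diary sent every night.

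**The concern.** The entry rule depends on what happens after randomisation. A participant may stop in the first 2 weeks because of poor tolerance, lack of effect, non-adherence, a cardiac event or a serious adverse reaction. Treatment can influence each of these, and cardiac events belong to the disease under study. A set selected in this way compares people who stayed on medication for 2 weeks, not the groups that were randomised, although it is presented under intention-to-treat.

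The protocol also gives two answers for one person. Someone who withdraws on day 10 is in the final analysis under 2.5 and outside the full analysis set under 2.16. A plan should not leave that choice open until the data are seen.

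**Working it through.** **1. The rules side by side.** For a voluntary dropout:
- Day 10: section 2.5 puts the last data into the analysis; section 2.16 excludes the participant from the full analysis set. The two conflict.
- Day 16: section 2.5 puts the last data in; section 2.16 admits the participant and carries the last observation forward. The two agree.

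**2. Inputs (section 2.11).** Treatment mean 1.90 per week (SD 0.45), reference mean 2.55 (SD 1.03), difference 0.65, two-sided 5%. The plan's total reproduces: 30/(1 − 0.20) = 37.5, rounded up to 38 per arm, 76 in all. The 20% allowance is 38 × 0.20 = 7.6 per arm.

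**3. Assumptions.** The protocol gives no early-stop rate. Let k = 1, 2 or 4 of 38 stop before week 2 in one arm and none in the other; k = 4 is about half the allowance. Suppose the full analysis set shows 0.65.

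**4. Danlou (DLT) stoppers keep a fraction f of the benefit.** Difference in all randomised = 0.65 × [1 − (1 − f)k/38]; overstatement = 0.65/difference − 1.
- f = 0: 0.633, 0.616, 0.582; overstated by 3%, 6%, 12%.
- f = 0.5: 0.641, 0.633, 0.616; overstated by 1%, 3%, 6%.
- f = 1: 0.65; no bias.

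**5. Placebo stoppers are 1 SD worse** (2.55 + 1.03 = 3.58). Difference in all randomised = 0.65 + 1.03k/38 = 0.677, 0.704, 0.758. Understatement = 1 − 0.65/difference = 4%, 8%, 14%. Placebo stoppers at the placebo mean change nothing.

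**6. No drug effect, DLT stoppers 1 SD worse.** DLT mean in the full analysis set = (38 × 2.55 − 3.58k)/(38 − k) = 2.522, 2.493, 2.429. The spurious difference from 2.55 is 0.028, 0.057, 0.121. A two-sided Welch test with SD 1.03 in both arms and sample sizes 38 − k and 38 rejects in 5.2%, 5.6% and 7.8% of trials.

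**7. The same null model with stops in both arms.** With 4 DLT stops against 0, 2, 3 and 4 placebo stops, type I error is 7.8%, 5.8%, 5.2% and 5.0%.

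**8. Power with all 76 analysed.** Welch test, 38 per arm, p = k/38. DLT variance = (1 − p) × 0.45² + p × 1.03² + p(1 − p) × [(1 − f) × 0.65]².
- No early stops: 0.94.
- f = 0, k = 1, 2, 4: 0.92, 0.90, 0.85.
- f = 0.5, k = 1, 2, 4: 0.93, 0.92, 0.89.

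These figures use SDs of weekly frequency, because section 2.11 gives none for the change from baseline.

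**The case against.** The best defence is that the 2-week mark matches the schedule. Table 3 lists angina frequency at day 0, week 2 and week 4, and section 2.15 enters outcomes in the case report form at those times. For a stop before week 2, the only scheduled value is baseline, and carrying it forward gives a change of zero. The protocol does not offer this as its reason, and it would not make the rule intention-to-treat. The nightly diary can supply earlier data, but the plan must then say how a few diary days become a weekly rate. A reader might infer that full outcome data already exist for early stoppers; the schedule does not show that.

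Three other stronger readings also lack support:
- That every stop after week 2 stays in. The last-data sentence in 2.5 concerns dropouts. Nothing says that participants removed under 2.5 or 2.6 remain in the full analysis set, so the contradiction is shown for voluntary dropouts only.
- That the primary analysis is biased. Section 2.16 does not name the primary set. The full analysis set is the natural candidate, but that is an inference.
- That type I error will be near 7.8%. That figure needs four DLT stoppers, none on placebo, each 1 SD worse, and no drug effect. In a 4-week, placebo-controlled trial with daily reminders and background therapy continued, such imbalance is possible but not shown to be likely.

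The size figures also take true week-4 values for stoppers, which carried-forward diary data need not equal.

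**Conclusion.** The rule is wrong as written. It is a stated rule, not a detail left to an analysis plan. The word only is absent, but a sole entry rule plainly excludes those who do not meet it.

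The bias can run in either direction. It depends on a difference between arms in the number or the angina course of early stops, neither of which the protocol lets one predict. The figures of 12% overstatement, 14% understatement and 5.2% to 7.8% type I error are one-arm extremes on assumed counts of up to 4 of 38. With few or balanced stops the effect is small or nil. The change should be made because the rule is inconsistent with the protocol's own principle and cheap to correct, not because large bias has been shown.

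**What to change.** In section 2.16, write: the full analysis set is all randomised participants, by allocated arm, regardless of time on medication, including those removed under 2.5(1) to (4) or 2.6. Keep the 2-week condition for the per-protocol set only.

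In sections 2.5, 2.6 and 2.12, state that after study drug stops the nightly diary and the week-4 assessment continue unless consent is withdrawn. Where week-4 data are still missing, use the last available diary data, as attacks per day scaled to a week; this carries out what 2.5 and 2.16 already intend. Add one sensitivity analysis of the missing values.

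The cost is protocol wording and follow-up of a few participants off drug, with a diary and a visit that already exist. There are two downsides. The effect may be diluted: power is about 0.92 with one DLT stopper who gets no benefit and 0.85 with four, against 0.94 with none. And some self-reported diary data will come from a few unblinded participants, which the report should identify by arm.

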**Methods and analysis::**

This study is a WeChat-based randomized, double-blind, and placebo-controlled clinical trial in China. Eligible participants are adults (aged 30–75 years) with CT-confirmed stable angina and traditional Chinese medicine-diagnosed intermingled phlegm and blood stasis syndrome. A total of 76 participants will be randomly allocated in a 1:1 ratio to the oral Danlou tablet group (1.5 mg a time, 3 times daily for 28 days) or the placebo group. Patients are permitted concomitant use of routine medications during these 28 days. The primary outcome is angina frequency per week. The secondary outcomes include angina severity, angina duration, traditional Chinese medicine efficacy, the withdrawal rate of emergency medications, blood lipids, and electrocardiograph efficacy. The WeChat app will be used to remind patients to take their medicines and fill out the forms. All data will be recorded in case report forms and analyzed by Statistical Analysis System software.

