#### Primary and secondary outcomes

2.8.1

All participants will be required to record the frequency, severity, and duration of angina in the “angina treatment diary.” The “angina pectoris diary” will be presented in the form of an electronic questionnaire, which will be sent to the patients every night via WeChat. The primary outcome is the change in the frequency of angina attacks from baseline to week 4. Secondary outcomes include the severity and duration of angina attacks, TCM efficacy, the withdrawal rate of emergency medications, blood lipid efficacy, and ECG efficacy. The severity of angina will be reported on the basis of the Visual Analogue Scale and the Canadian Cardiovascular Society score (1–2 points, only chest distress, no chest pain; 3–4 points, presence of angina during strenuous ordinary activity; 5–6 points, presence of angina during ordinary activities after meals, in the cold, in the wind, under emotional stress, or during the first few hours after waking up; 7–8 points, having difficulties walking 1 or 2 blocks or climbing one flight of stairs, at normal pace and under normal conditions; 9 to 10 points, no exertion needed to trigger angina). Angina duration refers to the time between the initial onset of symptoms to the time of remission. TCM efficacy is reported on the basis of the Curative Effect of Traditional Chinese Medicine on Coronary Heart Disease Stable Angina issued in 2018.^[30]^ The withdrawal rate of emergency drugs is calculated as follows: withdrawal rate = (number of tablets before treatment − number of tablets after treatment)/(number of tablets before treatment) × 100%. Emergency drugs mainly include nitroglycerin and the SuxiaoJiuxin Pill (another common emergency medicine in China). Blood lipids refer to total cholesterol, triglyceride, low-density lipoprotein–cholesterol, and high-density lipoprotein–cholesterol levels. The ECG efficacy standards are based on the Evaluation Criteria for Efficacy of Coronary Heart Disease Angina Pectoris and ECG (see Table 2). Among these indicators, the angina-related outcomes are derived from the electronic “angina treatment diary,” and other indicators are derived from the CRF. The data collection schedule is shown in Table 3.

**Table 2 T2:** ECG efficacy criteria.

Criteria	ECG changes
Marked effect	The ECG returns to “substantially normal” or reaches “normal ECG.”

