### Sample size estimation

2.11

As the trial is a superiority trial, we use the non-zero null test in Power Analysis and Sample Size (version 11) for sample size estimation. In a previous study,^[31]^ the mean (and standard deviation) of the angina frequency in the treatment group was 1.90 ± 0.45 per week, and that in the reference group was 2.55 ± 1.03 per week. We wanted to make the most conservative estimate, so we considered the superiority margin as 0 and the true difference as 0.65. Based on a 2-sided test size of a level of 5% (*α* = 0.05), a power of 90% (*β* = 0.1), and equal sample sizes in the 2 groups (*n*_1_:*n*_2_ = 1:1), our study will require 27 participants in each group. We adjusted the sample size of each group to 30. Considering a dropout rate of maximum 20%, the final sample size was estimated to be 76 participants.

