## Discussion

3

This study is a WeChat-based block-randomized, double-blind, placebo-controlled, parallel-group clinical trial with the aim of investigating the efficacy of DLT on stable angina. DLT is a Chinese proprietary medicine for the treatment of “intermingled phlegm and blood stasis syndrome” in CAD. Nitroglycerin is usually applied for the acute phase of angina attacks, while long-acting nitrates and trimetazidine are utilized for the relatively stable period. DLT is taken 3 times per day, just like the latter. DLT has been proven effective in clinical trials, animal experiments, cell experiments, pharmacology studies, a metabolomics study, and a network pharmacology study. However, previous clinical studies of SAP may have limitations with respect to randomization, allocation concealment, blinding, and so on. Moreover, previous studies took therapeutic effective rates calculated from ECG efficacy, angina pectoris scores, and TCM syndrome scores as the primary outcomes. Different evaluation standards and study designs lead to greater systematic error. Therefore, we will choose angina frequency as the primary outcome for this study, as it quantitatively, objectively, and specifically reflects the treatment efficacy. Moreover, we will evaluate the degree of coronary artery stenosis by dual-source CT angiography and exclude patients who are diagnosed with myocardial infarction or have a stent implantation, in order to reduce selection bias and confounding factors and to ensure compliance with the patients’ inclusion criteria.

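### Baseline adjustment is used only if imbalance is seen, and the primary outcome is a change in one place and a weekly level in others: precision is given up and room for choice is left

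*Protocol article*

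**What the plan says.** **Tests (section 2.16).** Adjustment is conditional: "analysis of covariance will be conducted in the case of important baseline non-comparability". No criterion for importance and no covariate is named. Otherwise the test follows the observed distribution. Data judged normal go to an unadjusted Student t test, and for the rest: "Non-normally distributed quantitative data will be presented as median and interquartile range and analyzed by the Kruskal–Wallis test". A paired t test is added that "will be used to analyze significant differences between pre- and post-treatment".

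**Primary outcome.**
- Section 2.8.1: "The primary outcome is the change in the frequency of angina attacks from baseline to week 4".
- Abstract, Methods and analysis: "The primary outcome is angina frequency per week".
- Section 2.11 (sample size) plans on weekly levels: "the mean (and standard deviation) of the angina frequency in the treatment group was 1.90 ± 0.45 per week", against 2.55 ± 1.03 in the reference group.
- Discussion: "we will choose angina frequency as the primary outcome for this study", which fits either reading.

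**Baseline data.** Table 3 schedules anginal frequency on day 0 as well as at weeks 2 and 4.

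**The concern.** In a randomised trial an observed baseline imbalance is a chance event. Whether it occurs says little about whether adjustment is worthwhile. What matters is how strongly baseline frequency predicts week-4 frequency, and that is unrelated to the imbalance in the particular sample. A rule that waits for an imbalance therefore discards a useful covariate in most trials. With about 30 evaluable patients per arm there is little precision to spare.

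The outcome wording matters for a separate reason. Unadjusted, a week-4 level and a change from baseline have different variances and give different p-values from the same data. They also need different sample sizes. The sample size is built on one and section 2.8.1 defines the other, so the planned power need not apply to the stated primary outcome, and a reader of the final report could not tell which comparison had been fixed in advance.

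The paired tests compare each arm with itself. A significant pre–post fall in the Danlou arm would not separate the drug from placebo response, background treatment or natural variation.

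**Working it through.** **Inputs from section 2.11.** Difference 0.65; SDs 0.45 and 1.03; two-sided 5%; power 90%; 27 per group, raised to 30; 76 in total after 20% dropout.

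**Assumptions, not in the document.** Correlation r between baseline and week 4 of 0.3, 0.5 or 0.7; equal SDs at the two times; imbalance declared at baseline p<0.05.

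**1. The plan's own figure.** SD = √((0.45² + 1.03²)/2) = √(1.2634/2) = 0.795, about 0.8. Then n = 2(1.960 + 1.282)² × 0.6317/0.4225 = 31.4, so 32 per group (33 by t test). The stated 27 is not reproduced; it matches a one-sided 5% t test. The dropout step does reproduce: 30/0.8 = 37.5, so 38 per group and 76 in total. The alpha question is a separate matter. What counts here is that the calculation uses levels and that 30 evaluable per arm gives 88.6% power on the level (normal approximation).

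**2. Closed-form power at 30 per arm.** The SD that drives each analysis is:
- week-4 level: SD
- change: SD × √(2(1 − r))
- ANCOVA: SD × √(1 − r²)

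Example, change at r = 0.3: SD = 0.795 × √1.4 = 0.940; SE = 0.940 × √(2/30) = 0.243; 0.65/0.243 − 1.96 = 0.72, so power is 76.3%.

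| r | Level, unadjusted | Change, unadjusted | ANCOVA |
|---|---|---|---|
| 0.3 | 88.6% | 76.3% | 91.3% |
| 0.5 | 88.6% | 88.6% | 95.5% |
| 0.7 | 88.6% | 98.3% | 99.3% |

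Level and change agree only at r = 0.5, where 2(1 − r) = 1. The ANCOVA to change variance ratio is (1 − r²)/(2(1 − r)) = (1 + r)/2, that is 0.65, 0.75 and 0.85.

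**3. The conditional rule, simulated.** Normal data, 30 per arm, SD 0.8, difference 0.65, at least 3,000 trials per setting; t test unless baseline p<0.05, then ANCOVA.

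| r | Rule on change | Rule on level | ANCOVA always |
|---|---|---|---|
| 0.3 | about 76% | about 87% | about 90% |
| 0.5 | about 88% | about 88% | about 94% |
| 0.7 | about 98% | about 89% | about 99% |

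The rule hardly differs from no adjustment, because the assumed trigger fires in only 5% of trials.

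**4. Type I error.** On one fixed outcome the rule gives about 3.5% to 5%. If both unadjusted t tests were run and the better reported, the two statistics correlate at √((1 − r)/2) = 0.59, 0.50 and 0.39, which gives 8.8%, 9.1% and 9.4%. If the better of the rule's two results were reported, it is about 7% to 8%.

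**5. Skewed data.** With log-normal data at r = 0.5, and with Kruskal–Wallis used when a Shapiro–Wilk test gives p<0.05 (assumed), the rule has 94.1% power on change and 97.2% on level, against 92.1% for parametric ANCOVA. At r = 0.3 the rule on change has 85.8% against 89.1%.

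**The case against.** **The stronger reading.** A reader might infer that the primary p-value is picked after the data are seen and that false positives are inflated. The document does not support that. Section 2.16 states a rule, an independent statistician applies it, and the steering committee meets before database lock. On one fixed outcome the rule stays at or below about 5%. The figure of about 9% needs an analyst who runs both outcome versions and reports the better one, and no such step is described.

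**The abstract merely condenses.** A one-line abstract may name the variable and leave the metric to section 2.8.1. That is fair for the abstract and the Discussion. It does not explain the sample size, which works from levels and would need its own SD for a change.

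**The power loss rests on assumptions.** This is correct. Neither r nor an imbalance threshold is in the document. The largest gap (76% against 90%) occurs only for change at r = 0.3. On the level at r = 0.3 it is two or three points, and on change at r = 0.7 about one. With skewed counts, which are plausible near two attacks a week, Kruskal–Wallis can match or beat parametric ANCOVA. A general loss of power is therefore not established.

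**The paired tests are harmless.** The article does not say that they support the efficacy claim, and between-group tests are specified separately. How often the placebo arm would show a significant fall depends on an assumed drop. With SD of change 0.8 and 30 patients it is 10% at 0.1 per week, 51% at 0.3 and 91% at 0.5. No single figure should be relied on; only the labelling needs attention.

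**An unseen analysis plan may settle it.** It could supply the threshold and covariates. Adjustment would still be conditional, and the article's outcome definition and sample size would still differ.

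**Conclusion.** The point holds as one of efficiency and consistency, not of error control. Making ANCOVA wait for an observed imbalance is a poor choice when the baseline value is already in hand. Under approximate normality, always adjusting is more powerful than the rule on either outcome version, by about 1 to 14 percentage points for 30 per arm over r from 0.3 to 0.7. That range depends on the assumed r, equal SDs, common SD of 0.8 and p<0.05 trigger; with skewed data the gain over Kruskal–Wallis may be nil or reversed. The mismatch between the change in section 2.8.1 and the levels in section 2.11 is in the text whatever is assumed, and is enough to leave the primary comparison open. This should be corrected, but it does not invalidate the design: an unadjusted randomised comparison of one fixed outcome remains valid.

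**What to change.** 1. Name one primary outcome, week-4 weekly angina frequency, in the same terms in the abstract, section 2.8.1 and section 2.11.
2. In section 2.16, make the primary analysis an ANCOVA with treatment and baseline weekly frequency, always fitted whatever the observed balance or normality, and report the adjusted difference with its 95% CI. Once baseline is a covariate, the treatment estimate is the same whether the response is week-4 frequency or change, so the two definitions no longer give different answers.
3. Keep a rank-based or count model as a fixed sensitivity analysis, which covers skewed data without letting the data pick the primary test.
4. Label the within-arm paired tests descriptive, not evidence of efficacy, or drop them.

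The cost is protocol and analysis-plan wording, as a dated amendment before unblinding. No new data or visits are needed, since day-0 frequency is already scheduled.
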